## 2.5 Participants

### 2.5.1 Eligibility criteria

Women with singleton pregnancies who are found to have cervical length <25 mm on transvaginal ultrasound between 14+0 weeks' gestation (dated by ultrasound or LMP and adjusted for ultrasound estimated date of delivery once ultrasound performed if no miscarriage prior to dating ultrasound) until 23+6 weeks' gestation with written consent to participate and one or more of the following risk factors;

History of:

- Previous preterm premature rupture of the fetal membranes ( $\leq 37$  weeks')
- History of previous PTB/second trimester loss ( $\geq 16$  weeks' or  $\leq 37$  weeks' gestation).
- Any cervical procedure to treat abnormal smears i.e. large loop excision, laser conisation, cold knife conisation or radical diathermy.
- Incidental finding of a short cervix on ultrasound scan (e.g. at the time of anomaly scan).

### 2.5.2 Exclusion criteria

- Women with persistent fresh vaginal bleeding evident on speculum examination.
- Women with visible membranes evident on speculum examination or open cervix on ultrasound scan.
- Women with severe abdominal pain/evidence of sepsis (as judged by attending clinician).
- Known significant congenital or structural or chromosomal fetal abnormality.
- Suspected or proven rupture of the fetal membranes at the time of recruitment.
- Women currently using progesterone pessaries or who have taken progesterone, for the purpose of preventing preterm birth, beyond 14 weeks gestation.
- Women who have a cervical suture *in situ* (vaginal or abdominal)
- Women who already have a cervical pessary *in situ*.
- If the attending clinician feels that an individual woman is more suited to one treatment modality over another
- Insufficient understanding of the trial in the opinion of the Investigator
- Any contraindications or cautions to the investigational medicinal product including:
  - known allergy or hypersensitivity to progesterone.
  - hepatic dysfunction,
  - undiagnosed vaginal bleeding,

[figure not shown]

- mammary or genital tract carcinoma,
- thrombophlebitis,
- thromboembolic disorders, • cerebral haemorrhage,
- porphyria.

### **2.5.3 Concomitant medication**

Participants will be permitted to use any concomitant medication (aside from the other study products themselves) required alongside the study drug/procedure/device. They will be enquired about and recorded at every visit. Any other medication or treatment that would form normal clinical management for these women at risk of preterm labour, i.e. antibiotics, corticosteroids, tocolytics, etc. will be permitted according to local hospital guidelines and clinician preference.

## **3 Recruitment**

### **3.1 Identification of participants**

Cervical length measurement is performed routinely at participating centres for women at high risk of preterm birth. It is measured using transvaginal ultrasound by a trained practitioner. Three measurements will be taken with a transvaginal probe (mm). Patient must have an empty bladder. The lowest of 3 measurements would be taken as final length (as per accepted clinical protocols).

High risk pregnant women who are found to have a cervical length of <25 mm during attendance at high risk surveillance antenatal clinic (hereafter referred to as prematurity surveillance clinic) will be identified. Their case notes will be reviewed for the patient's potential in to the trial and eligible patients will be informed of the study at time of diagnosis of short cervix. Members of the research team (midwives, doctors and scanning practitioners) will be familiar with the study so can discuss the research with women when required.

If a participant does not consent to sample collection (CVF, saliva, blood), or if the study site does not have the facilities to collect and process samples, this does not preclude trial entry. Eligible patients may be recruited from the ongoing NIHR funded Insight study (which includes biomarker measurement). If so, samples should only be collected once and can contribute to both studies. Valid consent will be obtained to permit data from samples can be shared between the Insight and Support databases.

### **3.2 Consent of participants**

All participants will be provided with a written patient information leaflet with verbal translation available for non-English speaking women (via Language Line where available). Women will be consented by an appropriately trained (GCP) doctor. All women will be provided an opportunity to discuss the research with one of the research team if requested.

Women will be given information about the study and will be allowed adequate time (up to 48 hours, depending on length of cervix and urgency of treatment, as determined by the attending clinician) to read the patient information sheet and invited to consider participation. The original consent form will be kept in the Investigator Site File, a copy will be given to the participant to keep and a copy kept in the hospital notes. The patient's case records must be noted to show that they are participating in this trial.

### **3.3 Study visit 1: Randomisation and intervention (14+0-23+6 weeks' gestation)**

At time of recruitment women will be randomly assigned (1:1:1) to cerclage, progesterone or pessary. Randomisation will be carried out online via the Medscinet web portal ([www.medscinet.net](http://www.medscinet.net)). Users will be assigned a personal identifier number. Due

[figure not shown]

to the nature of the interventions, the study is not blinded to the clinician or patient. Recruiters and trial coordinators will not have access to the randomisation sequence. Women will be informed at time of recruitment to which arm they have been randomised. A 'minimisation' procedure, using a computer-based algorithm, will be used to avoid chance imbalances in important stratification variables. Stratification variables will be a) gestation, b) BMI <30 or >30 kg/m^2 c) risk factor (previous premature delivery <24 weeks & previous cervical surgery). Women will not know what treatment they will be allocated prior to recruitment. Medscinet will write the randomisation program and hold the allocation code. Contact information will be obtained from the patient. Demographic measures will be entered into the central trial database. Following randomisation, the obstetrician will then arrange for the intervention to be performed as the randomisation indicates. There is no 'emergency code break' procedure as the trial is an open label RCT.

### 3.4 Investigational medicinal products

It is unlikely that the participants will be affected by a serious adverse event or a serious adverse reaction in this trial. The medical and surgical interventions they will be receiving are those which would be offered routinely in clinical practice.

#### 3.4.1 Cervical cerclage

The cerclage procedure will be booked at the time of recruitment. It will be performed (according to local practice and procedures) within 7 days of recruitment to the trial. A vaginal cerclage will be inserted in the operating theatre by a clinician trained in the procedure, according to the technique preferred by the clinician. It is usually inserted under regional anaesthetic. Tocolysis, antibiotics and antenatal corticosteroids can be considered at the clinician's preference, but will be documented and considered in the analysis. The patient will usually go home the same day and will be followed up with two to four weekly transvaginal ultrasound scans (or more frequent if clinically indicated) according to local protocols. The suture is removed easily by exposing the cervix and cutting the knot, usually without the need for anaesthetic. This is done electively when a woman is 37 weeks' gestation, or if she presents in symptomatic preterm labour before labour becomes established, to avoid cervical trauma. The suture should also be removed if there is clinical evidence of chorioamnionitis. Cervical cerclage insertion is an established surgical procedure, which is associated with minimal risks. These include infection, miscarriage, bleeding, difficulty with suture removal and preterm prelabour rupture of membranes.

#### 3.4.2 Vaginal progesterone

No significant adverse events have been reported with 200 mg vaginal progesterone. Vaginal progesterone once daily will be prescribed at the time of recruitment. Patients will be informed to insert vaginal progesterone every day until 34 weeks' gestation (or delivery, whichever is soonest). The patient will usually be followed up with two to four weekly transvaginal ultrasound scans (or more frequently if clinically indicated) according to local protocols. If the cervix shortens and membranes are visible, prior to 24 weeks' gestation, a rescue cerclage will be inserted, according to local protocols. Vaginal progesterone will be stored as per manufacturers instructions and dispensed by the hospital pharmacy. Licensed indications are for adjunctive use with oestrogen in post-menopausal women with an intact uterus (HRT). Progesterone will not be used within its licensed indications for this study. Any preparation of vaginal progesterone (200 mg) currently used in clinical practice for the prevention of preterm birth, will be allowed for use in the trial (eg Cyclogest, Uterogestan) according to individual site clinical protocols.

Contraindications are:

- known allergy or hypersensitivity to progesterone.
- severe hepatic dysfunction,
- undiagnosed vaginal bleeding,
- mammary or genital tract carcinoma,
- thrombophlebitis,
- thromboembolic disorders, • cerebral haemorrhage,
- porphyria.

[figure not shown]

If unexplained, sudden or gradual, partial or complete loss of vision, proptosis or diplopia, papilloedema, retinal vascular lesions or migraine occurs during therapy, the drug should be discontinued and appropriate diagnostic and therapeutic measures instituted. Vaginal progesterone 200mg should be used cautiously in patients with conditions that might be aggravated by fluid retention (e.g. hypertension, cardiac disease, renal disease, epilepsy, migraine, asthma); in patients with a history of depression, diabetes, mild to moderate hepatic dysfunction, migraine or photosensitivity and in breast-feeding mothers. Any adverse events experienced should be recorded as per the AE/ SAE section 8 of this protocol.

Indications for stopping treatment are:

- Elective (preterm) delivery
- Fetal membrane rupture
- Symptomatic placenta praevia
- Sudden or gradual, partial or complete loss of vision,
- Proptosis or diplopia
- Papilloedema
- Other patient reaction or sensitivity to progesterone
- Patient request

No dosage adjustments are permitted. Women recruited will be at high risk of early delivery and therefore likely to be highly motivated to comply with treatment. We will monitor compliance carefully by asking local staff to review medication packs. Patients will be asked to return any unused medication at a 34 weeks' visit (or after delivery) whichever soonest, which will be recorded in the online database. If progesterone has been stopped for reasons other than those listed above it can be restarted at any time up to 34 weeks of gestation.

This trial is deemed by the Sponsor to be a Type A trial as the IMP is used routinely with no higher risk to the patient than standard medical care. All drugs will be supplied from pharmacy stock in standard packaging. No clinical trial labelling is required and no trial specific prescription is required unless stipulated by individual sites.

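### The progesterone restart rule points back to a stopping list that omits two events, retinal vascular lesions and migraine, for which the same section calls for discontinuation

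*Protocol*

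**What the plan says.** Everything at issue is in the protocol, section 3.4.2 (Vaginal progesterone), which contains four relevant pieces of text, in this order.

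- A list of eight contraindications. It includes "severe hepatic dysfunction", "undiagnosed vaginal bleeding" and "mammary or genital tract carcinoma", together with allergy to progesterone, thrombophlebitis, thromboembolic disorders, cerebral haemorrhage and porphyria.
- A narrative sentence on events during treatment. It begins with visual loss, proptosis and diplopia, and ends: "papilloedema, retinal vascular lesions or migraine occurs during therapy, the drug should be discontinued".
- A bulleted list introduced by "Indications for stopping treatment are". Its eight bullets are elective (preterm) delivery, membrane rupture, symptomatic placenta praevia, loss of vision, proptosis or diplopia, papilloedema, other reaction or sensitivity to progesterone, and patient request.
- The restart rule: "If progesterone has been stopped for reasons other than those listed above it can be restarted at any time up to 34 weeks".

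Elsewhere, section 3.7 (Withdrawal from study) gives the investigator a right to take a woman off the drug in her best interest. Section 2.5.2 (Exclusion criteria) excludes women with contraindications at entry. Section 8.2.4 (Treatment stopping rules) deals with ending the trial, not with an individual's drug.

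**The concern.** The restart rule is permissive by default: whatever is not on the list it refers to may be followed by a restart. Such a rule is only as safe as that list is complete. Here the bulleted list repeats most of the discontinuation sentence but not all of it, so an event can be a reason to discontinue in one paragraph and a reason after which restart is allowed in the next.

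This is a safety instruction for the only drug arm. A site that follows the restart sentence literally could re-expose a woman after an event for which the same section tells it to discontinue. A site that follows the discontinuation sentence might not. The protocol gives neither site a means of settling the question.

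The matter is not one usually left to a statistical analysis plan. It is a treatment rule that the protocol itself states.

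**Working it through.** There is no figure to reproduce. The check is a comparison of the lists in section 3.4.2.

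**Step 1. Discontinuation sentence against stopping list.**

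| Event in the discontinuation sentence | On the stopping list? |
|---|---|
| Loss of vision | Yes |
| Proptosis | Yes (shared bullet) |
| Diplopia | Yes (shared bullet) |
| Papilloedema | Yes |
| Retinal vascular lesions | No |
| Migraine | No |

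Of 6 events, 4 are carried over and 6 − 4 = 2 are not.

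**Step 2. What the restart sentence refers to.** Its back-reference names no list. The bulleted list is the nearest one before it, and the only one headed as reasons for stopping. It is introduced with 'are', whereas the corresponding pessary list in section 3.4.3 is introduced with 'include', so it reads as exhaustive. The natural reading is therefore that the reference is to the bullets.

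**Step 3. Consequence.** On that reading, a stop for a retinal vascular lesion or migraine is a stop for an unlisted reason, and restart is permitted up to 34 weeks. The one route by which the bullets could still cover these events is the item on other reactions or sensitivity to progesterone. That route requires the site to attribute the event to the drug. The discontinuation sentence does not ask for attribution; it speaks of unexplained events.

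**Step 4. Contraindications against stopping list (secondary).** Only allergy or hypersensitivity is covered, through the same reaction bullet. The other 8 − 1 = 7 are absent: severe hepatic dysfunction, undiagnosed vaginal bleeding, mammary or genital tract carcinoma, thrombophlebitis, thromboembolic disorders, cerebral haemorrhage and porphyria. The section does not say whether a contraindication that arises on treatment is a stopping reason, or how the restart sentence then applies. Bleeding is a foreseeable case: section 8.2.2 mentions it among the reasons for admission with symptoms of preterm labour, while the stopping list has only symptomatic placenta praevia.

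**Step 5. Patient request.** This is one of the bullets, so by implication a woman who paused by choice falls outside the restart permission. The text does not state a prohibition.

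**Step 6. Who is exposed.** With 540 women allocated 1:1:1, 540 / 3 = 180 are assigned progesterone. Treatment runs from as early as 14+0 weeks to 34 weeks, so for at most 34 − 14 = 20 weeks. The protocol gives no rate for any of these events, so the number of women affected cannot be estimated.

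**The case against.** The best reply is that the restart sentence does not single out the bullets. The contraindications, the discontinuation sentence and the bullets all stand above it in the same section. If the back-reference takes in all three, the rule permits nothing that the section forbids. That reading is available, and it is why the fault is put here as a conflict on the natural reading and not as an explicit permission. But a safety rule should not depend on which of three preceding texts a site takes it to mean.

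A reader might infer more than the documents support, in four ways.

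- *That the protocol allows restart after a thromboembolic event or any other contraindication.* A contraindication list and a stopping list serve different purposes and need not match. A woman who develops a contraindication meets the section's own warning against the drug, and the restart sentence, which only says the drug can be restarted, does not claim to override it. What stands is silence on how the two interact.
- *That migraine has contradictory statuses throughout the section.* Caution in women with migraine or a history of it is compatible with discontinuing when migraine occurs on treatment. The firm conflict is only its absence from the stopping list.
- *That a woman who stops at her own request is permanently barred.* This is implied, not stated.
- *That the trial's results are affected.* No event rates are given, the analysis is by intention to treat (section 5), and no effect on the endpoint is shown.

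Two mitigations are real but partial. Sites may use the reaction bullet for either omitted event, but only after attributing it to progesterone. The investigator's discretion under section 3.7 is a right to discontinue; it does not limit restart, although a clinician may of course decline to restart.

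**Conclusion.** The point stands in a limited form. Two of the six events for which section 3.4.2 calls for discontinuation are missing from its stopping list, and the restart sentence, read against that list, permits restart after both unless the site attributes them to progesterone. This rests on taking the back-reference to mean the nearest list and the only one headed as reasons for stopping. If it was meant to cover everything earlier in the section, the conflict disappears but the wording is still ambiguous.

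The absence of 7 of 8 contraindications from the stopping list is a gap in what the section says about events arising on treatment, not a contradiction. The position of patient request is likewise an implication that needs to be made explicit.

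The gain from correction is that sites apply one participant-safety rule in the same way. No view is taken on which clinical rule is right.

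**What to change.** Reconcile the discontinuation sentence, the stopping list and the restart sentence in section 3.4.2 so that they name the same events. Replace the unspecific back-reference in the restart sentence with a reference to a named list. Have the clinical team divide the stopping reasons into those after which restart is allowed and those after which it is not, and state where contraindications arising on treatment and patient request belong. Which event goes in which group is for the clinical team; none is proposed here.

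The cost is a wording amendment to the protocol and a memo to sites. No additional participants, visits or procedures are needed.

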### **3.4.3 Cervical pessary**

The product must be stored at room temperature. The appropriately sized (see appendix 1) pessary will be inserted within 7 days of recruitment by the attending clinician, who will be trained in the procedure. They will be given detailed written instructions about its subsequent management. It will be removed by a trained clinician at 37 weeks' gestation (or in the event of established labour). The patient will be usually be followed up with two to 4 weekly transvaginal ultrasound scans (or more frequent if clinically indicated) according to local protocols. If the cervix shortens and membranes become visible prior to 24 weeks' gestation, a rescue cerclage will be inserted, according to local protocols

Indications for stopping treatment include:

- Pessary dislodges or falls out twice or more
- Patient request

There might be some increase in vaginal discharge, however there is no evidence to suggest increased risk of infection or other complications.

### **3.5 Pre- and Post intervention biomarker measurement**

At a convenient time between randomisation and intervention, the following procedures will take place in order to obtain biomarker levels (if study site facilities allow and the participant has consented to them):

[figure not shown]

- a) One sterile speculum examination and approximately 4 cervico-vaginal swabs (high vaginal and/or endocervical). The speculum examination will last approximately 20-30 seconds (normally 15 seconds if only 1 swab is taken as per routine clinical care after 18 weeks'). qfFN will be performed from 18 weeks' gestation.
- b) A saliva sample (5 ml) will be obtained.
- c) Two blood samples will be taken (2 x 15 ml/1 tablespoon), one for genetic analysis; one for biomarker analysis.

CVF sampling will be repeated, if facilities allow, at each subsequent routine clinic visit until 28 weeks' gestation. Sample collection is not mandatory for trial participation. Some women may only want to provide samples at a single visit or only provide one or more of the samples listed.

### 3.6 Subsequent study visits

All participants will be seen in a follow up appointment, normally between 2 and 4 weeks post-intervention. Subsequently, all follow up visits will be at the discretion of the attending clinician. Each visit will be documented on the online database. A transvaginal ultrasound cervical length measurement should be performed, and results recorded on the trial database, at each visit. At each visit, information will be obtained on compliance, adverse events or pregnancy complications.

The final study visit will take place between 34+0 and 38+0-weeks' gestation. Patients randomised to progesterone will be asked to return all unused medication and empty blister packs, in order to collect compliance information. Patients randomised to pessary will return at 37 weeks for removal. Patients randomised to cerclage will be seen between 34 and 37 weeks, and an appointment made for removal in the appropriate clinical area (usually hospital birth centre). If delivery has occurred prior to this time, then study staff will contact the participants, to arrange a follow up visit and collection of unused medication. Other than the baseline post intervention visit and final study visit, all other trial visits will be times to routine clinic attendances according to local clinical protocols and clinician practice. Interim study data will therefore only be collected if the patient attends the appropriate department for routine purposes.

Note review will take place 28 days after delivery to capture to collect maternal, fetal and health economic data up until 28 days postnatal. A contact/visit with the participant is not required.

### 3.7 Withdrawal from study

Participation in the study is voluntary. A patient has the right to discontinue drug/pessary or completely withdraw from the study at any time for any reason. The Investigator has the right to discontinue a patient taking drug/pessary at any time if it is deemed to be in the patient's best interest. If a participant elects to withdraw from the study no further samples will be collected. Identifiable data or tissue already collected with consent would be retained and used in the study if the women consents for it to be so. Consent would be sought to collect use the participant's delivery details (if delivery has not yet occurred). If a participant who has given informed consent loses capacity to consent, the participant would be withdrawn from the study. Identifiable data or tissue already collected with consent would be retained and used in the study. No further data or tissue would be collected or any other research procedures carried out on or in relation to the participant. If the participant is withdrawn due to a serious adverse event, the Principal Investigator will arrange for follow-up visits or telephone calls until the event has resolved or stabilised. However as the participants are pregnant women data will be collected routinely to outcome (i.e. delivery) and used in the analysis unless the consent to collect the outcome is specifically refused by the participant.

If an eligible patient is excluded or refuses to participate, the reasons for this will be documented where possible for input into trial metrics.

[figure not shown]

